## Abstract

**Rationale:**

The clinical impact of a novel mechanical thrombectomy strategy, which integrates distal access with flow reversal and flow arrest via a distal balloon, all within a single procedure [Safety and Efficacy of the overall throMbectomy system for sTroke (SEMTiC) strategy], has not been tested.

**Aim:**

The SEMTiC-01 study is the first prospective, multicenter *in vivo* study evaluating the safety and efficacy of the combined thrombectomy system—iNedit, iNdeep, and iNtercept—in patients with acute ischemic stroke.

**Sample size estimates:**

The study was designed with a sequential structure based on the efficacy endpoint (eTICI ≥2b) reported in the literature [71.1% with a 95% confidence interval of (68.5%, 73.8%)]. An interim analysis was set for 115 patients and a final analysis for 225 patients, ensuring 98% power at a one-sided 0.025 significance level, with a 2.6% non-inferiority margin and a 15% assumed withdrawal rate.

**Design:**

SEMTiC-01 is a prospective, multicenter, single-arm, open-label clinical safety and efficacy investigation.

**Outcome:**

Primary efficacy endpoint: expanded treatment in cerebral infarction score (eTICI) ≥2b revascularization within ≤ 3 stent retriever passes. Primary safety endpoint: monitoring serious adverse events within 24 h post-intervention and all-cause mortality at 90 days.

## Introduction

Mechanical thrombectomy (MT) for large vessel occlusion (LVO) strokes has been the subject of multiple randomized clinical trials, which have invariably demonstrated its overwhelming efficacy (1).

The initial key trials (2–5) focused on MT within 6 h of onset. However, the DEFUSE 3 (6) and DAWN (7) studies extended the therapeutic window to 24 h for selected patients with late-onset or wake-up strokes. Their findings were included in the 2018 American Heart Association (AHA)/American Stroke Association (ASA) stroke guidelines (8). MT can be performed with or without prior rt-PA (2).

Currently, significant research efforts are focused on improving the techniques available for performing MT.

Two main techniques for MT are stent retrievers and direct aspiration catheters, often used in combination. Stent retrievers, the most common (3), can be paired with a balloon guide catheter (BGC) to arrest and reverse blood flow during thrombus removal (9). However, the BGC is usually only advanced to the extracranial carotid artery for balloon inflation. There are no currently available mechanical devices that feature a balloon catheter near the distal tip, which can be inflated in the intracranial portion of the vessel. This could potentially increase the system's stability as the balloon would be surrounded by the petrous segment of the carotid encased in bone.

Direct aspiration catheters, while comparable to stent retrievers in terms of achieved revascularization (10), are less commonly used. They can be operated manually or with an aspiration pump via distal access catheters (DACs), with flexible tips for strong aspiration and efficient clot removal. However, they lack flow arrest and do not feature a balloon to improve the system's stability.

The iVascular (Sant Vicenç dels Horts, Barcelona) neurothrombectomy devices, including the iNedit balloon distal access catheter, iNdeep microcatheter, and iNtercept stent retriever, are designed to leverage the benefits of temporary proximal blood flow restriction via a balloon located 5 cm from the catheter tip, providing enhanced stability during distal aspiration. These devices are compatible with all commonly used stent retrievers.

Preliminary results on using the iNedit balloon DAC in different clinical scenarios indicate that the device achieved a high first-pass effect and final recanalization rate with no safety concerns, resulting in a high percentage of favorable clinical outcomes (11).

This study aims to evaluate the efficacy and safety of this novel MT approach (SEMTiC strategy), which uniquely combines distal access, flow arrest, and flow reversal in a single procedure for acute ischemic stroke (AIS) patients. The non-inferiority of this combination will be compared to existing literature data.

## Methods and analysis

### Design

SEMTiC-01 is a prospective, multicenter, single-arm, open-label clinical safety and efficacy investigation.

### Study population

In the SEMTiC-01 trial, eligible participants are AIS patients treated within 24 h of symptom onset, defined as the last time the patient was seen well (LTSW; the start of the procedure is defined as arterial puncture time). Patients will be enrolled at 18 sites, which are in Spain (14 sites: Hospital Clinic Barcelona, Hospital Universitario de Bellvitge, Hospital Universitario Central de Asturias, Hospital Reina Sofía de Córdoba, Hospital Vall d'Hebron, Hospital Clínico San Carlos, Hospital German Trías i Pujol, Hospital Universitario de Cruces, Hospital General Universitario de Alicante, Hospital Universitario la Fe, Hospital Universitario General de Canarias, Hospital General Universitario Gregorio Marañón, Hospital Universitario de Badajoz, and Hospital Clínico Universitario de Valencia), Germany (3 sites: K. München Hospital, K. Nürnberg Hospital, and K. Ludwigsburg Hospital), and Belgium (1 site: AZ Groeninge Hospital) between July 2022 and June 2024.

The detailed inclusion/exclusion criteria are listed in Table 1.

**Table 1 T1:** Study inclusion and exclusion criteria.

**Inclusion criteria**
**Clinical**
1. Age ≥ 18 years.
2. Informed consent signed by the patient or their representative to use the patient's data.
3. Focal disabling neurological deficit consistent with acute cerebral ischemia.
4. Baseline NIHSS obtained before the procedure of ≥6 points and ≤25 points.
5. Pre-stroke mRS score ≤2.
6. Planning to start treatment within 24 h of symptoms onset, defined as the LTSW (the start of the procedure is defined as arterial puncture).
**Neuroimaging criteria**
1. Occlusion (TICI 0 or TICI 1) of the internal intracranial carotid artery, M1 and M2 segments of the middle cerebral artery, and T carotid artery, suitable for mechanical thrombectomy confirmed by conventional angiography.
2. For patients treated ≤8 h:
a) Score 6–10 on Alberta Stroke Program Early CT Score (ASPECTS).
For patients treated between 8 and 24 h:
a) “Target Mismatch Profile” on CT perfusion or MRI (ischemic core volume was <70 mL, mismatch ratio was >1.8, and mismatch volume was >15 mL).
3. Ability to obtain selective angiography by catheterization of the target artery.
**Exclusion criteria**
**Clinical**
Initially treated with a different thrombectomy device in the same procedure.
1. Patient had suffered a stroke in the past year.
2. Occlusion (TICI 0 or TICI 1) in vertebrobasilar territory.
3. Clinical symptoms suggestive of bilateral stroke or stroke in multiple territories.
4. Known hemorrhagic diathesis, coagulation factor deficiency, or oral anti-vitamin K anticoagulant therapy with an INR > 3.0.
5. Blood glucose <50 or >400 mg/dL. Note: If blood glucose could be successfully reduced and maintained at an acceptable level by administering the medication recommended by the European Stroke Organization (ESO) in its guidelines, the patient might be included.
6. Severe sustained hypertension (systolic pressure >185 mm Hg or diastolic pressure >110 mm Hg). Note: If blood pressure could be successfully reduced and maintained at an acceptable level by administering the medication recommended by the ESO in its guidelines (also IV infusion of antihypertensives), the patient might be included.
7. Serious advanced or terminal illness with an anticipated life expectancy of <6 months.
8. History of life-threatening allergy (more than rash) to contrast medium.
9. Known allergy to nickel, prior to treatment.
10. Known renal insufficiency with creatinine ≥3 mg/dL or glomerular filtration rate (GFR) <30 mL/min.
11. Cerebral vasculitis.
12. Known current cocaine use.
13. Patient who was participating, at the time of inclusion, in a study with a device or drug that could affect this study.
14. Patients who were unlikely to be available for 90-day follow-up (e.g., no fixed home address and visitors from overseas).
**Neuroimaging criteria**
1. CT or MRI evidence of hemorrhage (the presence of microbleeds was allowed).
2. Significant mass effect with midline shift.
3. Evidence of complete occlusion, high-grade stenosis, or arterial dissection in the extracranial or petrous segment of the internal carotid artery (tandem lesions).
4. Patients with known or suspected underlying intracranial atherosclerotic lesions responsible for the target occlusion.
5. Patients with occlusions in multiple vascular territories (e.g., bilateral anterior circulation or anterior/posterior circulation).
6. Evidence of intracranial tumor except for asymptomatic meningiomas with no mass effect.

### Treatment devices

#### SEMTiC strategy

This approach leverages an innovative balloon distal design, where a balloon located a few centimeters from the catheter tip blocks blood flow, while the distal tip enables aspiration. This technique uniquely integrates distal access, flow reversal, and flow arrest—via the distal balloon—into a single procedure.

##### iNedit

The iNedit balloon distal access catheter is a double-lumen coaxial catheter from the connector to the balloon and a single lumen from the balloon to the tip. It is designed with braid and coil reinforcement. The distal segment has a compliant occlusion balloon located 5 cm from the tip of the catheter, the purpose of which is to occlude the flow at the discretion of the operator, if deemed necessary during the procedure.

The catheter's proximal “Y”-shaped luer-lock connector has a side port for balloon inflation/deflation with diluted contrast and a straight port for device passage or aspiration. The outer diameter of the catheter is compatible with access systems with a minimum internal lumen of 0.088” (2.235 mm). The maximum volume of balloon inflation is 0.2 mL.

##### iNdeep

The iNdeep microcatheter is a single-lumen catheter from proximal to distal shaft, reinforced with braid and variable stiffness through its entire length to ensure optimal trackability. At the most distal end, there is a radiopaque marker that helps to visualize the device under fluoroscopy.

The catheter's distal body has a durable hydrophilic coating for easier navigation through tortuous arteries and is available in three internal diameters (0.017”, 0.021”, and 0.027”).

##### iNtercept

The stent retriever consists of a self-expanding nitinol basket with proximal and distal markers for fluoroscopic positioning and gold markers to assess deployment. It is supplied compressed in an introducer sheath for easy insertion via a microcatheter. After full deployment, the device is deployed within or beyond the thrombus and retracted under suction.

### Standard protocol approvals, registration, and patient consent

The SEMTiC-01 trial is registered on clinicaltrials.gov (NCT05893719). The protocol and data collection of the trial have been approved by the Hospital Clinic, Barcelona, the ethics committee, and all participating sites. Written informed consent will be obtained from patients or representatives before inclusion into the trial.

### Patients inclusion

All patients were consecutively included when the interventional neurologist confirmed that they met all the inclusion criteria and would treat them with the proposed strategy (SEMTiC strategy), including the use of all three devices. In cases where successful reperfusion (defined as eTICI 2b-3) was not achieved after three passes with the iNdeep, iNedit, and iNtercept devices [all with European Conformity (CE) market], rescue therapy—defined as the use of any additional strategies or devices—was permitted.

Deferred informed consent was utilized to prevent delays in treatment initiation. Once a patient is considered eligible for the study, the patient or their representative receives the “Patient Information Sheet” and “Informed Consent Form” (ICF). Written consent will be required from the patient or a family member during the study period to authorize the use of patient data. Investigators will explain the study and deliver a copy of the signed ICF. Each consented patient will be assigned a unique identifier, composed of a site number and a sequential patient number, based on the order of inclusion at each site.

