### Primary outcomes

#### The primary efficacy endpoint

The primary efficacy endpoint is the achievement of a successful neurothrombectomy, defined as a revascularization of grade ≥2b-3 with ≤3 passes on the eTICI scale (12). The Core Lab used the eTICI scale to assess the performance of the overall system.

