### Statistical analysis

All data will be analyzed with SPSS 27.0 Software. The mean ± standard deviation (SD) will be used if the data are normally distributed, and the median and interquartile range (IQR) will be used if the data are non-normally distributed.

The proportion of patients with eTICI ≥ 2b will be obtained, and the significance level for non-inferiority will be determined using the *Z* statistic for comparing two proportions with a non-inferiority margin of −0.026.

All values will be estimated using the 95% confidence interval (recommended Wilson's or Agresti methods). The following study populations will be defined for statistical analysis:

Intention to treat (ITT) is defined as all patients included in the study who have been treated with at least one of the study devices. The primary efficacy analysis in relation to non-inferiority will be performed on this population.Population by protocol (PP) is defined as ITT subset with no major deviations from the clinical investigational plan. The primary efficacy analysis in relation to non-inferiority will also be performed with this population.Modified population by protocol (PP) is defined as PP subset excluding patients treated with rescue therapy.

All outcomes will be evaluated across all study populations. The proportion of patients undergoing rescue therapy will also be measured. The impact of rescue therapy on both angiographic and clinical outcomes will be assessed using adjusted logistic regression models. A subgroup analysis will compare the results achieved in cases with the occlusion of the M2 vs. the M1/T carotid segments.

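### The protocol conflicts with itself on when a patient is included; if inclusion waits for the deferred consent signature, entry to the ITT set can depend on the outcome

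*Protocol article*

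**What the plan says.** All references are to the protocol article.

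- **Table 1, clinical inclusion criterion 2:** "Informed consent signed by the patient or their representative to use the patient's data".
- **Standard protocol approvals, registration, and patient consent:** "Written informed consent will be obtained from patients or representatives before inclusion into the trial".
- **Patients inclusion, on the moment of inclusion:** "All patients were consecutively included when the interventional neurologist confirmed that they met all the inclusion criteria". The same sentence adds that the operator intends to use the study strategy, so this moment comes before treatment.
- **Patients inclusion, on consent:** "Deferred informed consent was utilized to prevent delays in treatment initiation". The signature has no closer time limit than the study period: "Written consent will be required from the patient or a family member during the study period to authorize the use of patient data".
- **Patients inclusion, on identifiers:** "Each consented patient will be assigned a unique identifier".
- **Statistical analysis, ITT:** "all patients included in the study who have been treated with at least one of the study devices". The per-protocol set is a subset of ITT, and the modified per-protocol set is a subset of that.
- **Primary efficacy endpoint:** "defined as a revascularization of grade ≥2b-3 with ≤3 passes on the eTICI scale", assessed by the Core Lab.
- **Primary safety endpoint:** serious adverse events within 24 h, and mortality at 90 days.

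**The concern.** ITT membership requires that a patient be included, and the article gives two incompatible answers to when that happens. One is before treatment, when the operator confirms eligibility. The other is when the signature required by criterion 2 exists, and deferral allows that to come after the procedure.

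Under the second answer, the angiogram that determines the primary efficacy endpoint already exists when it is settled whether the patient counts. Early serious adverse events or death may also have occurred. If consent is refused or never obtained more often after a poor course, the patients lost would tend to be the unfavourable ones. Core Lab reading does not protect against this, because the selection happens before a case reaches the analysis set. All three populations are drawn from included patients, so comparing them would not reveal it. In a single-arm comparison with a literature rate, no concurrent group undergoes the same selection.

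At stake are the ITT success rate, on which non-inferiority rests, and the 90-day mortality figure.

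**Working it through.** **1. The statements side by side**

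| Source | Inclusion occurs | Consistent with deferred consent? |
|---|---|---|
| Table 1, criterion 2 | once consent is signed | only if inclusion may follow treatment |
| Approvals section | after written consent | only if inclusion may follow treatment |
| Patients inclusion, opening sentence | when the operator confirms all criteria, before treatment | no, because criterion 2 may still be unmet |
| Patients inclusion, identifier sentence | not stated; identifier goes to consented patients | a treated patient without consent has no identifier |

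If inclusion is at the operator's confirmation, ITT is fixed before the outcome, but criterion 2 and the approvals section are then breached whenever consent is deferred. If inclusion is at signature, criterion 2 and the approvals section hold, but ITT entry can follow the outcome. The two readings can give different denominators.

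**2. The reported result**

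Inputs:
- Reference rate 71.1% (95% CI 68.5% to 73.8%), margin 2.6 points, one-sided 0.025 (Abstract; Sample size determination).
- ITT success 80% at the 115-patient analysis (Trial status).
- Assumption: the ITT denominator is 115. Then 0.80 × 115 = 92 successes. (91/115 = 79.1% and 93/115 = 80.9% do not round to 80%.)

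Bar: 71.1% − 2.6% = 68.5%. Critical Z: 1.96. Standard error of the reference from its interval: (0.738 − 0.685)/(2 × 1.96) = 0.0135.

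The article does not specify the variance for Z, so three forms are shown for 92/115:
- Null variance: (0.800 − 0.685)/√(0.685 × 0.315/115) = 0.115/0.0433 = 2.65
- Observed variance: 0.115/√(0.80 × 0.20/115) = 0.115/0.0373 = 3.08
- Allowing for reference uncertainty: 0.115/√(0.0373² + 0.0135²) = 2.90
- Wilson 95% lower limit: 71.8%

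All four clear the bar, so the stated non-inferiority reproduces.

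**3. Adding back k treated, unconsented patients, all failures: 92/(115 + k)**

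| k | Rate | Z, null variance | Z, observed variance | Z, with reference SE | Wilson lower limit |
|---|---|---|---|---|---|
| 4 | 92/119 = 77.3% | 2.07 | 2.29 | 2.16 | 69.0% |
| 5 | 92/120 = 76.7% | 1.93 | 2.12 | 2.00 | 68.3% |
| 6 | 92/121 = 76.0% | 1.78 | 1.94 | 1.83 | 67.7% |

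Non-inferiority is lost at k = 5 (null variance, Wilson) or k = 6 (the other two). As shares of those treated: 5/120 = 4.2% and 6/121 = 5.0%.

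**4. If half of the unconsented patients were successes: (92 + k/2)/(115 + k)**

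At k = 16: 100/131 = 76.3%, null-variance Z = 1.93, so non-inferiority is lost. At k = 15, Z = 1.97 and it still holds. The share is 16/131 = 12%.

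**5. At N = 225, all added patients failures**

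- At an 80% rate (180/225), 17 to 19 are needed, depending on the variance: 17/242 = 7.0% to 19/244 = 7.8%.
- At the planning rate of 82% (184/225), 22 to 24 are needed: 22/247 = 8.9% to 24/249 = 9.6%.

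**The case against.** The opening sentence of Patients inclusion describes consecutive inclusion before treatment, and the information sheet is handed over once the patient is considered eligible. On that reading ITT is fixed before the outcome and consent governs only data use. Deferred consent is a defensible choice in emergency stroke care with CE-marked devices. This objection stands in part: deferral itself is not at fault, and the favourable reading is available. It does not remove the conflict with criterion 2 and the approvals section.

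A reader might infer several stronger things that the article does not support:

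- **That patients did enter ITT only after their outcome was known.** This is one of two printed readings.
- **That patients who deteriorate or die leave no trace.** A representative or family member may sign at any time in the study period, and nothing says that death blocks entry or that site logs are lacking.
- **That unconsented patients are primary failures.** Families would react to clinical state rather than pass count. Rescue therapy is permitted after three passes, so some primary failures may end well reperfused. The direction of bias is plausible, not shown.
- **That a few patients would overturn the trial.** Five to six applies only at 115 patients and only if all failed.
- **That the 15% withdrawal allowance measures lost consent.** The article uses it for sample size and does not link it to consent.

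Handling of non-consent may be set out in the full investigational plan, so its absence here is not the complaint. The contradiction in the printed text is.

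**Conclusion.** The point holds as a contradiction with a possible bias. The article does not fix when a patient is included, and one reading of its own words lets ITT entry depend on events after treatment. Neither the direction nor the presence of bias is established, because the number treated without consent is not given.

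The possible size is not negligible for the only non-inferiority result reported: 4 to 5% of treated patients in the worst case, about 12% if half were successes. The final analysis is sturdier, at roughly 7 to 10% in the worst case. These figures assume that the ITT denominator is 115 at the first analysis, that the rate is 80% or 82% at N = 225, and that non-inferiority is judged at one-sided 0.025 against 68.5%.

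**What to change.** 1. Reconcile inclusion criterion 2, the approvals section and Patients inclusion so that they state one moment of inclusion.
2. Define ITT as all patients in whom a first study device was introduced, whenever consent was signed. This stays close to the present device-based definition and precedes the outcome.
3. From site logs, report the number treated with a study device but without consent, with reasons (refused, died before consent, no representative available).
4. Add a tipping-point or worst-case sensitivity analysis of the primary efficacy endpoint counting these patients as failures. Where ethics approval allows, add one of 90-day mortality counting deaths before consent.

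Recruitment ended on 30 June 2024, so identifiers can no longer be assigned prospectively at device introduction. Outcomes of patients who did not authorise use of their data may be unusable; the count alone still supports the efficacy tipping-point analysis. If the count is zero, one sentence settles the matter.

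The cost is revised wording, a log review at the 18 sites and a little extra analysis. The success rate and mortality may come out slightly less favourable.

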### Completion of the study

All patients treated (with the study device or rescue therapy) were evaluated at 24, 72 h, or discharge and 90 days after the index procedure. The patient's study participation is considered complete at the 90-day visit.

